### Procedures

#### Inclusion Criteria

Participants are eligible for enrollment if they are (1) aged 18 years and older; (2) self-identify as LGBT+ using local, culturally appropriate self-identifications [10,57,79]; (3) reside in one of the two cities (Bangkok and Mumbai); (4) able to understand and willing to provide informed consent; and (5) able to understand primary language(s) at the site (Thai, Hindi/Marathi, or English). We do not use exclusion criteria based on mental health. The Patient Health Questionnaire-2 (PHQ-2) will be administered in the baseline survey; those with scores indicative of clinical depression (≥3 on the depression scale) will be referred by peer counselors to in-house mental health professionals on call at the site.

#### Recruitment

Participants will be recruited online with electronic flyers and social media messages developed with CBO partners, through CBO social media accounts in WhatsApp groups, e-groups, virtual LGBT+ groups, Facebook, and a study website linked to all CBOs to reach potentially eligible participants.

#### Randomization

Participants will be randomized to the immediate intervention group or waitlist control group (12-week waitlist) at a 1:1 ratio, stratified by sex and gender [83] (cisgender men, cisgender women, transgender and gender nonbinary people), with a computer-generated sequence. Participants and researchers will not be blinded; in the informed consent process, potential participants will be told about the waitlist control.

#### Informed Consent

Immediately upon screening into the study, potential participants will be shown an informed consent form online and given time to read through it. Potential participants will be instructed to contact the study coordinator and provided with an email address if they wish to ask any questions or request clarifications before providing consent.

### Intervention

#### Overview

As there is no manualized intervention for COVID-19 prevention, we adapted efficacious eHealth interventions for HIV, the largest pandemic of the last century, by members of our research team [79,84]. The 3 primary outcomes—increasing COVID-19 knowledge, protective behaviors, and reducing psychological distress—are central to public health approaches to halt SARS-CoV-2 transmission [85,86].

#### Motivational Interviewing and Psychoeducation

The intervention builds on evidence-based eHealth interventions using motivational interviewing (MI) [87,88] and psychoeducation [89] approaches to increase health knowledge, behaviors, and reduce psychological distress [90-94]. Several MI-based studies have been conducted with LGBT+ people [95-97], including in India [79,84] and Thailand [98]. MI is a client-centered counseling approach that elicits and strengthens intrinsic motivation for change [87,99,100]. MI is based on Stages of Change theory, which enables tailoring to individual readiness for change with an emphasis on supporting client autonomy and volition [101,102]. Psychoeducation integrates education and counseling to promote mental health [89]. Consonant with MI, it is a strengths-based approach in which clients are considered partners in treatment [89]. Psychoeducational techniques are used to mitigate barriers to comprehending complex and emotionally laden information, with a focus on developing strategies to use the information proactively, such as in anticipating actions if one were to experience distress or loneliness [88].

#### Peer Counselor Training

Peer counselors will receive an initial 3-day online training along with a 2-day booster training immediately preceding the intervention. Training will be conducted by study coordinators and agency staff in each site, covering COVID-19, public health–recommended protective behaviors, pandemic stress (ie, anxiety, depression, social isolation), MI-based counseling, psychoeducation, and research ethics [78,103]. Training will include online small-group discussions, role-playing, and mock sessions, with peer counselor feedback also used to fine-tune the intervention.

#### Intervention Group

We use a 3-session peer-delivered MI-based brief counseling (45 minutes to 1 hour) format with weekly individual sessions, which has previously demonstrated effectiveness in interventions for alcohol, tobacco, and marijuana use, and HIV prevention [79,104-107]. Peer counselors will complete session-specific checklists (activities conducted, issues encountered, self-evaluated quality of engagement) following each session. To assess fidelity, supervisors will review a random selection of peer counselors’ initial sessions, which will be digitally recorded, and provide feedback using a structured checklist. Supervisors will conduct biweekly online group discussions to provide feedback, emotional support, and discuss and troubleshoot challenges to protocol implementation. In each online session, participants will complete a 4-item survey to evaluate content, satisfaction with the session and its duration, and any exposure to other interventions. Peer counselors write up brief counseling notes after each session, along with the brief self-evaluation. We use process evaluation to assess dose and implementation fidelity [107].

#### Waitlist Control Group

Governments and public health ministries in India and Thailand provide almost daily briefings about COVID-19 via multiple sources: TV, newspapers, Facebook, WhatsApp, LineChat, Instagram, and SMS text messages. Online messenger platforms (eg, WhatsApp, Line) provide LGBT-targeted information, with additional government mobile apps developed for general populations. The waitlist control group will receive brief reminders by mobile phone to support retention.

#### Assessments

Each participant will complete a baseline survey, a postintervention survey 2 weeks after their final eHealth session, and a follow-up survey 2 months after the postintervention survey. Waitlist controls will complete a second baseline survey immediately before beginning the eHealth intervention.

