**Methods:**

SafeHandsSafeHearts is a 2-site, parallel waitlist-controlled RCT to test the efficacy of a 3-session, peer counselor–delivered eHealth intervention based on motivational interviewing and psychoeducation. The study methods, online infrastructure, and content were pilot-tested with LGBT+ individuals in Toronto, Canada, before adaptation and rollout in the other contexts. The primary outcomes are COVID-19 knowledge (index based on US Centers for Disease Control and Prevention [CDC] items), protective behaviors (index based on World Health Organization and US CDC guidelines), depression (Patient Health Questionnaire-2), and anxiety (Generalized Anxiety Disorder-2). Secondary outcomes include loneliness, COVID-19 stress, and intended care-seeking. We will enroll 310 participants in each city aged 18 years and older. One-third of the participants will be cisgender gay, bisexual, and other men who have sex with men; one-third will be cisgender lesbian, bisexual, and other women who have sex with women; and one-third will be transfeminine, transmasculine, and gender nonbinary people. Participants will be equally stratified in the immediate intervention and waitlist control groups. Participants are mainly recruited from online social media accounts of community-based partner organizations. They can access the intervention on a computer, tablet, or mobile phone. SafeHandsSafeHearts involves 3 sessions delivered weekly over 3 successive weeks. Exit interviews will be conducted online with 3 subgroups (n=12 per group, n=36 in each city) of purposively selected participants to be informed by RCT outcomes and focal populations of concern.

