### Statistical Analysis Plan

Intervention efficacy will be assessed by comparing data from the second preintervention baseline survey from the waitlist control with postintervention data from the immediate intervention group. The *χ^2^* test for unadjusted analyses and logistic generalized estimating equations (GEEs) for adjusted analyses [130] will be used to assess dichotomous primary outcomes (COVID-19 knowledge, protective behaviors, psychological distress). Sensitivity analyses will use composite scores of primary outcomes with independent-samples *t* tests for unadjusted analyses and GEEs (Gaussian or Poisson) for adjusted analyses. To assess if intervention efficacy is sustained, waitlist control data from the second preintervention survey will be compared with intervention group follow-up data. We will use intention-to-treat analyses and also report per-protocol analyses [131]. In addition to analyses of efficacy for LGBT+ people as a whole, the sample size is powered for a priori subgroup analysis (cisgender gay/bisexual men, cisgender lesbian/bisexual women, transgender and gender nonbinary people). We will assess if intervention effects on protective behaviors are mediated by increases in knowledge, self-efficacy, perceived vulnerability, and decreases in conspiracy theories and psychological distress, and if the effects on psychological distress are mediated by resilience.

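### Both surveys in the primary contrast are timed by participants' own engagement, so non-attenders and non-starters have no survey date and the intention-to-treat comparison risks arm-specific selection

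*Protocol article*

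**What the plan says.** Only the Assessments section of the protocol article sets the timing of the outcome surveys. It opens with "Each participant will complete a baseline survey" and continues with "a postintervention survey 2 weeks after their final eHealth session, and a follow-up survey 2 months after the postintervention survey". For the control arm it adds: "Waitlist controls will complete a second baseline survey immediately before beginning the eHealth intervention".

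The Statistical Analysis Plan section assesses efficacy by "comparing data from the second preintervention baseline survey from the waitlist control with postintervention data from the immediate intervention group". It compares the same waitlist survey with the immediate group's later follow-up to judge whether the effect lasts. On the analysis population it says: "We will use intention-to-treat analyses and also report per-protocol analyses".

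Two other statements matter for timing. The abstract's Methods paragraph says "SafeHandsSafeHearts involves 3 sessions delivered weekly over 3 successive weeks", and the Randomization section says "Participants will be randomized to the immediate intervention group or waitlist control group (12-week waitlist) at a 1:1 ratio". No outcome survey is given a date counted from randomisation.

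**The concern.** An intention-to-treat comparison needs an outcome from everyone randomised, collected on a schedule that does not depend on what participants do afterwards. Here the immediate-arm survey is triggered by that person's last session, and the waitlist survey by that person's start of the programme. Both triggers are post-randomisation behaviour, and they are different behaviours: attending sessions soon after allocation in one arm, and coming back to start after a long wait in the other.

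If the rule is followed literally, the people most likely to be missing are those who did not engage, and the filter differs between arms. Psychological distress is the most exposed outcome, because distress may plausibly be related to dropping out. The same two surveys carry the efficacy contrast for every primary outcome. An outcome that was never collected cannot be recovered at analysis.

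**Working it through.** **1. Whether each type of participant has a survey date under the Assessments text**

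| Participant | Trigger | Survey date |
|---|---|---|
| Immediate, all 3 sessions | own final session | defined |
| Immediate, 1 or 2 sessions | own final session | defined if this means the last session attended; undefined if it means session 3 |
| Immediate, no session | none | undefined |
| Waitlist, starts | start of programme | defined |
| Waitlist, never starts | none | undefined |

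The immediate arm's later follow-up is counted from its postintervention survey, so it inherits the same gap.

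**2. Timing among attenders.** Assume session 1 takes place at randomisation and sessions are weekly. The survey falls at (number of sessions - 1) + 2 weeks:
- 3 sessions: 2 + 2 = week 4
- 2 sessions: 1 + 2 = week 3
- 1 session: 0 + 2 = week 2

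Someone who stops after one session is thus measured 2 weeks earlier than a completer. The Study Design section calls the sessions biweekly, while the abstract and the Intervention Group section call them weekly. These passages must be reconciled, because the survey dates depend on them. Controls are measured at the end of a wait given as 12 weeks, so retention is tested over a longer span in that arm.

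**3. What the plan's own figures contribute.** The Sample Size Calculations section gives control rates of 40% (knowledge), 36% (handwashing) and 50% (depression), a 30% change, 80% power and two-sided alpha of .05. The formula is

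n per arm = [1.96 √(2p̄(1-p̄)) + 0.842 √(p1(1-p1) + p2(1-p2))]² / (p1-p2)²

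Reading 30% as percentage points:
- 40% vs 70%: 42 per arm, 84 in total
- 36% vs 66%: 43 per arm, 86 in total
- 50% vs 20%: 39 per arm, 78 in total

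This reproduces the stated range of 78 to 86. A relative 30% change would need 340 to 652. So the planned effect is 30 points. The section's 20% is an attrition allowance; it is not a rate of non-attendance or of non-starting, and the documents give neither.

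**4. Illustration of selection bias.** Assumed, not from the documents: no true effect, and depression of 45% in engagers and 70% in non-engagers. Let q be the share of non-engagers in each arm and d the share of the arm with no survey, all of them non-engagers. Then

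observed rate = [(1-q) × 45% + (q-d) × 70%] / (1-d)

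| Missing, immediate vs waitlist | q | Immediate | Waitlist | Spurious difference |
|---|---|---|---|---|
| 20% vs 20% | 20% | 45.0% | 45.0% | 0 |
| 20% vs 0% | 20% | 45.0% | (36 + 14)/1 = 50.0% | -5.0 points |
| 30% vs 10% | 30% | 45.0% | (31.5 + 14)/0.9 = 50.6% | -5.6 points |
| 40% vs 10% | 40% | 45.0% | (27 + 21)/0.9 = 53.3% | -8.3 points |
| 0% vs 20% | 20% | 50.0% | 45.0% | +5.0 points |

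The last row is the second with the arms exchanged: the sign follows whichever arm loses more non-engagers.

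**5. Illustration of dilution.** If 20% of the immediate arm does not engage and gains nothing (assumed), a 30-point effect among those who engage is 0.8 × 30 = 24 points among all randomised.

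**The case against.** The best defence is that the text describes timing and does not restrict who is surveyed. The sentence begins with each participant and sets no attendance condition. A partial attender has a last session to count from. The 12-week waitlist, or the calendar crossover period in Study Design, could date the control survey whether or not the person starts, and the Waitlist Control Group section provides reminders to support retention. The authors list per-protocol analyses separately, so they mean intention-to-treat to reach beyond adherent participants. Strengths and Limitations names differential attrition as a threat and offers the short programme and 2-week follow-up as mitigation. Survey windows and missing-data methods commonly sit in a full protocol or analysis plan that is not shown.

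Much of this stands, and it rules out stronger readings that a reader might infer:
- That non-engagers have no outcome. The article never says they go unsurveyed.
- That intention-to-treat cannot be done. It can, if everyone is in fact surveyed or missing outcomes are handled credibly.
- That the planned GEE needs data missing completely at random. With one endpoint per person, a correctly specified adjusted model remains valid if missingness depends only on arm and the included covariates.
- That the effect is necessarily overstated. Dilution acts that way, but selection can act in either direction.

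What the defence does not remove is the stated rule. The sentence that includes everyone also dates the survey by a session that some people will not attend. The 12-week wait could anchor the control survey, but the Assessments text anchors it to starting instead. The mitigation in Strengths and Limitations leaves both triggers in place. The point concerns data collection that the article does specify, and later modelling is a poor substitute for outcomes that could have been collected.

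**Conclusion.** The concern holds in a limited form. The two surveys in the primary contrast are timed by post-randomisation behaviour that differs between arms. As written, the schedule is undefined for immediate-group participants with no session and for waitlisted participants who never start, and it measures partial attenders earlier than completers. An analysis labelled intention-to-treat could therefore turn into a comparison of engaged participants with selection that differs by arm.

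The size and direction of any bias are not known from the documents. The illustrations of about -5 to -8 points for depression, and of 24 rather than 30 points for dilution, rest on assumed non-engagement rates and outcome differences. The bias illustration also requires unequal loss, which the documents do not show; equal loss of the same type of person gives no bias. The reason to act is that the affected surveys carry all primary outcomes and the remedy is cheap.

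**What to change.** Amend the Assessments section so that the outcome surveys in both arms are dated from randomisation, with one common target day and window. The day should be late enough for the immediate arm to have finished its sessions plus 2 weeks, and before the waitlist crosses over. State that the surveys go to every randomised participant, whatever sessions were attended and whether or not a waitlisted person starts, and analyse all as randomised. Date the immediate arm's later follow-up from randomisation as well. The sustained-effect comparison also uses the waitlist's pre-crossover survey, so that survey should be dated by the end of the wait and not by starting.

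The costs are:
- A protocol amendment while baseline assessment, allocation and intervention are underway, with three ethics approvals involved. Surveys already completed keep the old timing and should be identified as such.
- Some extra reminders, and possibly one more waitlist survey if the common day falls well before the end of the wait.
- An interval between last session and survey that varies slightly between participants.
- An effect in all randomised that may be smaller than the planned 30 points. With 20% non-attendance, no effect in non-attenders and full survey response (all assumed), power in a 103-person sex and gender group (51.5 per arm) would be about 69% for knowledge and handwashing and 72% for depression. City-wide power (154.5 per arm) would be about 99%. This reflects the effect of offering the programme and is no reason to keep the present timing.

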### Measures

#### Overview

Demographic data, including age, sex, gender identity, sexual orientation, city of residence, country of birth, education, and employment, will be obtained to determine the baseline equivalence of groups.

#### Primary Measures

##### Knowledge

COVID-19 knowledge [108,109] will be assessed using an index developed by the research team and based on published research [110,111].

##### Preventive Behaviors

Public health–recommended preventive behaviors [108,109] will be assessed using an index developed by the research team based on WHO and US Centers for Disease Control and Prevention guidelines.

##### Mental Health Measures

Depression and anxiety symptoms in the past 2 weeks will be measured using the PHQ-2 [112] and the Generalized Anxiety Disorder 2-item scale [113].

#### Secondary Measures

The indices assessed as secondary measures are listed in Textbox 1.

Secondary measures.UCLA Loneliness Scale [114]COVID Stress Scales (COVID danger, COVID traumatic stress) [115]Intended care-seeking [116]Unmet health care needs and perceived quality of care [117]COVID-19–related risk perception and testing (developed for this study)COVID-19 vaccines (developed for this study)Discrimination in Medical Settings Scale (DMS Scale) [118]Conspiracy beliefs [116,119-121]Attitudes toward government handling of COVID-19 [110]Support for government action regarding the pandemic [122]Alcohol Use Disorders Identification Test (AUDIT-C) [123]Sexual and reproductive health changes [124]Intimate partner violence changes [125]General and HIV-specific COVID-19 impacts [47,126]Household Water InSecurity Experiences (HWISE Scale) [127]Response to Stressful Experiences Scale (RSES-4) [128]Outness indicator [129]Technology ownership (developed for this study)

### Statistical Analysis Plan

Intervention efficacy will be assessed by comparing data from the second preintervention baseline survey from the waitlist control with postintervention data from the immediate intervention group. The *χ^2^* test for unadjusted analyses and logistic generalized estimating equations (GEEs) for adjusted analyses [130] will be used to assess dichotomous primary outcomes (COVID-19 knowledge, protective behaviors, psychological distress). Sensitivity analyses will use composite scores of primary outcomes with independent-samples *t* tests for unadjusted analyses and GEEs (Gaussian or Poisson) for adjusted analyses. To assess if intervention efficacy is sustained, waitlist control data from the second preintervention survey will be compared with intervention group follow-up data. We will use intention-to-treat analyses and also report per-protocol analyses [131]. In addition to analyses of efficacy for LGBT+ people as a whole, the sample size is powered for a priori subgroup analysis (cisgender gay/bisexual men, cisgender lesbian/bisexual women, transgender and gender nonbinary people). We will assess if intervention effects on protective behaviors are mediated by increases in knowledge, self-efficacy, perceived vulnerability, and decreases in conspiracy theories and psychological distress, and if the effects on psychological distress are mediated by resilience.

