### Study Design

We use a sequential quantitative-qualitative mixed methods design [74]. We will implement a 2-site, parallel waitlist-controlled randomized controlled trial (RCT) to test the efficacy of a 3-session, peer counselor–delivered eHealth intervention to increase COVID-19 knowledge and protective behaviors, and decrease pandemic-related psychological distress. The immediate versus waitlist allocation ratio is 1:1. We conducted a formative intervention development phase with LGBT+ individuals in Toronto to pilot test and refine the online study infrastructure (participant eligibility screening, randomization, survey programming and administration, databases, and dashboard interface for tracking and monitoring) and peer counselor training before rollout in the other 2 sites. All study materials were culturally and contextually adapted through consultation with experts in each site, pilot-tested among individuals from locally eligible study populations, and then revised before implementation.

The immediate intervention group to be enrolled over a 2-month period will complete the 3-session biweekly intervention from August to October 2021. The randomized waitlist control group will crossover to receive the intervention from October to December 2021, after the immediate group finishes. Waitlist control groups, often used in psychosocial interventions [75], avert ethical problems with no-treatment controls, particularly with groups that experience health disparities, moreover amid a pandemic, and also avoid alienating the community.

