We mitigate threats to internal validity due to differential attrition by implementing a brief, 3-session, weekly intervention with 2-week immediate follow-up, which reduces the waitlist time for the control group. There is a reduced risk of contamination as an eHealth intervention for which participants will be individually recruited online and participate online. This threat is also mitigated due to stay-at-home orders and physical distancing guidelines that deter or prevent attendance at CBO sites, although guidelines may change during the course of the intervention.

Finally, the unpredictable course of the pandemic, and regional and local variation in severity and public health responses, has delayed onset of the study and created intermittent barriers and interruptions in implementation. Nevertheless, the development and testing of the intervention during a pandemic may increase its feasibility and external validity. Once developed, implemented, and tested, the intervention may be more readily usable for LGBT+ and other marginalized populations in future pandemics and other emergency situations.

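### The primary contrast sets the immediate arm's early postintervention survey against a later waitlist survey, so secular pandemic change is counted as intervention effect, and the documents do not fix the size of the gap

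*Protocol article*

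**What the plan says.** All places are in the protocol article.

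- **Contrast.** The Statistical Analysis Plan section assesses efficacy by "comparing data from the second preintervention baseline survey from the waitlist control with postintervention data from the immediate intervention group". Whether the effect lasts is assessed by setting the same waitlist survey against the immediate arm's follow-up survey.
- **Surveys.** Assessments gives each participant a baseline survey, "a postintervention survey 2 weeks after their final eHealth session, and a follow-up survey 2 months after the postintervention survey". The waitlist arm has one extra survey, a second baseline taken immediately before its own sessions begin. Nothing is listed for that arm between its two baselines.
- **Wait.** Randomization describes a "waitlist control group (12-week waitlist) at a 1:1 ratio, stratified by sex and gender".
- **Sessions.** The Abstract (Methods) states that "SafeHandsSafeHearts involves 3 sessions delivered weekly over 3 successive weeks", and Intervention Group describes a "format with weekly individual sessions". Study Design instead says that the immediate group "will complete the 3-session biweekly intervention from August to October 2021".
- **Calendar.** Recruitment started on 1 August 2021 and data collection will likely be complete by 31 January 2022 (Abstract, Results). The immediate group is enrolled over 2 months. The waitlist arm crosses over from October to December 2021, once the immediate group has finished (Study Design).
- **Context.** Strengths and Limitations cites "the unpredictable course of the pandemic, and regional and local variation in severity and public health responses" as a source of delay and interruption, but does not connect it with survey timing.

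**The concern.** Randomisation balances who is in each arm. It does not balance when they are measured. If the control arm is surveyed weeks after the immediate arm, any change in the outcomes over those weeks enters the estimated effect, and it may inflate or mask a true one.

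The primary outcomes are COVID-19 knowledge, protective behaviours, and depression and anxiety over the past 2 weeks. All can plausibly move with waves of infection, rules and public messaging. Every primary outcome is exposed, because all use the same pair of surveys. Adjusting for baseline does not remove the problem, since change is then measured over different intervals in the two arms.

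**Working it through.** **1. Survey times from randomisation.** Let s be the weeks from randomisation to the first session and g the spacing of sessions in weeks. The article does not state s; I assume 0 or 1. Then

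- postintervention survey = s + 2g + 2
- follow-up survey = postintervention survey + 8.7 (2 months = 2 × 30.4375 / 7 weeks)
- waitlist second baseline = 12, if the stated wait is taken literally

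| Reading of the schedule | Postintervention survey | Gap to week 12 | Follow-up minus week 12 |
|---|---|---|---|
| Weekly (g = 1) | week 4 to 5 | 7 to 8 weeks | 0.7 to 1.7 weeks |
| Biweekly as every two weeks (g = 2) | week 6 to 7 | 5 to 6 weeks | 2.7 to 3.7 weeks |
| Biweekly as twice a week (g = 0.5) | week 3 to 4 | 8 to 9 weeks | −0.3 to 0.7 weeks |

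With a 12-week wait the control survey is 5 to 9 weeks late on every reading. The contrast meant for sustained effect is much closer in time.

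**2. Calendar windows with a 12-week wait.** Assume uniform enrolment from 1 August to 30 September 2021 (61 days) and weekly sessions. Postintervention surveys run from 29 August to 28 October (week 4) or 5 September to 4 November (week 5). Waitlist second baselines run from 24 October to 23 December. The overlap is 61 − 56 = 5 days (8%) or 61 − 49 = 12 days (20%). With sessions every two weeks it is 19 to 26 days (31% to 43%).

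**3. Does the stated calendar allow a 12-week wait?** Count back from 31 January 2022 with weekly sessions.

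- Minus 2 months: latest postintervention survey about 30 November 2021.
- Minus 2 weeks: latest final session about 16 November.
- Minus 2 more weeks: latest second baseline about 2 November.
- Minus 12 weeks: latest enrolment about 10 August.

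Someone enrolled on 30 September could wait only 33 days, about 5 weeks. Conversely, a 12-week wait from 30 September puts the second baseline at 23 December, the third session at 6 January and the follow-up at around 20 March 2022. That is past both the October to December crossover and the expected end of data collection. With sessions every two weeks, the count back reaches about 19 October for the second baseline and 27 July for enrolment, before recruitment began. The stated wait, crossover window, follow-up and end date therefore cannot all hold.

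**4. What remains if the wait is compressed.** Suppose weekly sessions start at randomisation and the waitlist arm starts after the immediate group's last session (30 September + 14 days = 14 October) but by 2 November. The mean immediate-arm survey date is the midpoint of 29 August to 28 October, which is 28 September. The waitlist surveys are then on average 16 to 35 days later. The gap shrinks but does not vanish.

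**5. Illustration of the consequence.** The article's Mumbai total reproduces: 36% vs 66% needs 43 per arm, so 86 in all; 86 × 1.2 = 103.2, taken as 103; 3 × 103 = 309. Completers per arm in one city are 309/2 × 0.8 ≈ 124. Take no intervention effect, 40% in one arm and 40% plus an assumed drift in the other, and the two-sided two-proportion z test at 0.05.

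- 5 points: pooled p = 0.425, null SE = √(2 × 0.425 × 0.575 / 124) = 0.0628, critical difference 1.96 × 0.0628 = 0.123. Rejection rate about 12%.
- 10 points: pooled p = 0.45, null SE = 0.0632, critical difference 0.124. Rejection rate about 35%.

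With both cities (618/2 × 0.8 ≈ 247 per arm) the rates are about 20% and 61%, but only if the drift is the same in Mumbai and Bangkok.

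**The case against.** **The size of the gap is a construction.** This stands. Week 4 to 5 is derived, not stated, and assumes a first session within about a week of randomisation. A reader might infer that the arms are measured exactly 7 to 8 weeks apart in almost separate calendar windows. That needs the 12-week wait to be taken literally, and step 3 shows that it conflicts with the stated end of data collection. That end date is itself given only as likely.

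**The trend could be modelled.** Both arms have untreated baselines through August and September. These overlap roughly the first half of the immediate arm's postintervention window. Together with the waitlist second baseline they give some untreated data on calendar trend, and the covariates of the adjusted GEE may be specified in a plan not shown. This stands in part. Such a model must assume the shape of the trend and that people enrolled at different times are comparable. It cannot supply the missing control measurement at the matched time from randomisation.

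**The drift sizes are hypothetical.** This stands. The documents give none, and the pooled rates need a common drift although the article itself notes regional variation.

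**Stronger readings that the documents do not support.** A reader might see a contradiction between the 12-week wait and the remark "with 2-week immediate follow-up, which reduces the waitlist time for the control group". That sentence concerns differential attrition and says only that a brief programme makes the wait shorter than it would otherwise be. A reader might also extend the point to the mediation analysis, because mediators and outcomes share one control survey. The immediate arm's postintervention survey shares that feature, so it is not evidence of a timing difference between arms.

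**Conclusion.** The concern holds in this form. The article fixes a primary contrast between surveys taken at different times from randomisation, with no control survey at the matched time. Followed as written, it attributes secular change to the intervention. This is a stated design choice, not a detail left to another document.

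With the stated 12-week wait the control survey is 5 to 9 weeks late, depending on session spacing and start. Time since randomisation is then aliased with arm, and calendar time largely so. If the wait is compressed to meet the stated end date, a smaller average displacement remains under the assumptions of step 4. The documents do not settle which applies.

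The false-positive rates of about 12% and 35% show what a 5- or 10-point drift would do in one city. They do not predict that such a drift occurred. Nor do the documents make the follow-up contrast exactly time-matched: day 89 against day 84 requires weekly sessions, the first session at randomisation and a full 12-week wait.

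**What to change.** 1. **Add a matched control survey.** Give waitlist participants who have not yet passed that point a short online survey of the primary outcomes, at the same time from randomisation as the immediate arm's postintervention survey. Make that the primary contrast. The cost is an amendment, a little survey burden and incomplete coverage, because enrolment and intervention were already under way when the article was written (Results).
2. **Where no matched survey exists**, label the current contrast non-contemporaneous. If the 12-week wait is kept, report immediate-arm follow-up against waitlist second baseline beside it as the comparison closer in time. It should be supportive only: it estimates an effect roughly 2 months after the postintervention survey, which is a different question and is exposed to more attrition.
3. **Reconcile the schedule.** The length of the wait, the crossover window, the follow-up for each participant and the end of data collection must be made consistent, as must weekly and biweekly sessions. State the resulting survey times from randomisation for both arms. This costs only text.
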